#### 11e. Dissemination of findings

The results of this study will be disseminated as widely as possible in South Africa, where new strategies for reducing pre-ART loss to follow up and promoting earlier treatment initiation are eagerly sought, and in other countries facing similar challenges. A full report will be made to the study site and other local stakeholders and will be circulated widely and posted on our website. We will also develop a short briefing document to send to the national and provincial departments of health, donor agencies, and other interested organizations, and we will present the results at relevant conferences in South Africa and internationally. One or more journal manuscripts will be submitted to an appropriate peer-reviewed international journal. Finally, a flier summarizing the results in lay language will be distributed to patients at the study site and posted in patient waiting areas, to ensure that study subjects and others gain access to the findings. (The flier will be submitted for IRB approval prior to distribution.)

### **12. Human Subjects Considerations**

#### 12a. Risks and protection against risks

For this study, we will not collect any biomedical samples that would not be collected as part of routine care, nor will we implement any clinical procedures that are not routinely carried out under standard of care. The rapid test technologies to be used in this study require exactly the same biological samples (blood, sputum) that would be required for routine care, and the technologies have all been validated and approved for use in South Africa. The strategy being evaluated merely accelerates the timing of events. All biomedical data for the study will be drawn from routinely collected medical records, including patient charts and laboratory reports. The only other new data generated for the study will be responses to questionnaires. We therefore believe that our study poses no physical risks to subjects beyond those routinely encountered. It may, however, pose risks associated with loss to HIV care, emotional distress, breach of confidentiality, and time loss.

##### *12a i. Loss to HIV care*

**Risk:** The study aims to initiate on ART patients who might otherwise be lost to HIV care. Some patients lost before or after ART initiation will seek care at other sites, but many will not and will postpone or end all HIV care and treatment, some until they become more seriously ill, others forever. Although the rapid initiation strategy is expected to increase the proportion of patients who do initiate ART, there is a possibility that patients who accept rapid ART initiation will subsequently discontinue treatment at a greater rate than do those who receive standard ART initiation. Preliminary studies in South Africa suggest that the loss of treatment-eligible patients before starting ART, which is expected to decrease as a result of the intervention, exceeds loss after initiation. It is also likely that patients who discontinue

treatment soon after rapid initiation may never have started at all, had only standard initiation been offered. We therefore expect the intervention to have a net positive impact on our primary outcome, the proportion of patients who are alive, in care, and virally suppressed 10 months after testing HIV-positive or making their first HIV or ANC care visit. We cannot be certain of this result in advance, however. Because this is an evaluation of routine practice and retention in care is a study outcome, no efforts will be made to retain patients in the study, beyond those already routinely undertaken by the study site clinic as part of standard of care.

**Protection:** As patients who are subjects of this research will be both those who remain in HIV care and those who drop out, and as the research team will have access to information about which subjects are lost, efforts must be made to return these patients to HIV care. However, since losses from HIV care are a primary outcome of this study, study staff cannot interfere with usual patient care. Upon enrollment in care at the site, patients are routinely asked to give a cell phone number and address where they can be contacted at and identify an acquaintance who can be contacted should they not be able to be reached through the previously listed means. The study site maintains a small team of loss-to-follow-up counselors trained in confidentiality and ethical issues around contacting patients. These counselors do not always have access to timely information about which patients have been lost, however. As we will be generating this data, we will work alongside to the counselors to make sure they have adequate, up-to-date information on study subjects' status and can attempt to contact the patients using standard clinic procedures if necessary. In particular, we will ensure that all patients defined as lost to follow up at their 6-month viral load monitoring visit (or by 10 months after study enrollment) are referred to the counselors to be contacted.

#### *12a ii. Emotional distress*

**Risk:** By necessity, the study population for this study will include patients who have been newly diagnosed with HIV. Interacting with them in order to explain the study and confirm eligibility before requesting written informed consent may cause some emotional distress for some potential subjects.

**Protection:** To minimize any emotional distress caused by interacting with study staff or enrolling in the study, we will train the site's staff to emphasize when they introduce the study to potential subjects that referral to study staff and enrolling in the study are completely voluntary and that those who do not wish to enroll will receive exactly the same care as the study site would otherwise have provided. Potential subjects will also be told that they can discontinue participation even after consenting and can revert to standard, non-study care at the study site at any time. Study staff will be trained to look for signs of emotional distress and instructed to terminate or postpone the enrollment process if subjects appear distraught.

#### *12a iii. Accidental disclosure of HIV status or other loss of confidentiality*

**Risk:** A potential risk of the study concerns the confidentiality of data about HIV status and treatment program enrollment. A high level of stigmatization continues to inhibit the disclosure of HIV status in the study population. Data collected in interviews or from clinic

records or the site's electronic database could be disclosed and reveal a person's HIV status. Additionally, the shopping vouchers received for study participation may cause others to assume participants are part of an HIV-related study if they are used at the store nearest to the clinic.

**Protection:** Several steps will be taken to protect subjects against the risk of accidental disclosure of HIV status. Individual documents (including signed consent forms, case report forms, and the linking file) which could associate patients with an HIV study will be kept strictly confidential. Signed consent forms will be stored in locked cabinets away from the study site, with access limited to the senior investigators. Paper case report forms will be stored separately from consent forms in a locked cabinet at the study team's office, which is itself located in a secure facility, or in a secure archiving facility. Scanned copies of the CRFs will not include identifiers and will be password-protected. The linking file will also be password-protected, with access limited to study staff. It will be used only for the purpose of linking study identification numbers with electronic medical records and, when necessary for data verification and completion, with paper-based patient files and source documents.

To protect study subjects from being assumed to be participating in an HIV-related study if they use the shopping voucher at the store nearest to the clinic, participants will be informed of this risk and given a list of other stores at which the voucher is redeemable. Store staff are not informed of the nature of this study and vouchers that participants receive do not differ in any way from shopping vouchers purchased for other reasons.

To protect against other violations of confidentiality, study staff will be trained in expectations that they are not to disclose any information collected in the study to anyone outside the study team. All study staff will be required to pass an ethics certification course, such as the on-line certification offered by the NIH. All participants will be encouraged to contact the HIV testing coordinator, principal investigator, or other staff to report any undesirable conduct associated with the study. These reports will be brought to the attention of the study site and the PI, and appropriate steps will be taken to solve the problems, including reporting to relevant ethical review boards.

#### *12a iv. Time loss*

**Risk:** Subjects participating in the study and assigned to Track 1 rapid initiation will be asked to remain in the study clinic for approximately 4-5 hours to allow all procedures to be completed. This is longer than they may otherwise be required to spend at the clinic and may be inconvenient for some subjects.

**Protection:** Potential subjects will be informed about the time requirements during the informed consent process. Those who wish to participate in the study but cannot remain in the clinic on the same day for the amount of time required will be able to delay treatment initiation until they find a time that is convenient for them, thus mitigating the inconvenience.

#### 12b. Benefits

##### *12b i. Direct benefits*

Study subjects offered rapid treatment initiation will benefit from the opportunity to start ART quickly and with fewer clinic visits and time delays than they would otherwise have incurred. Study subjects offered standard initiation will not receive any direct benefits from the study but will receive the same care that would have been provided in the absence of the study.

#### *12b ii. Indirect (societal) benefits*

The study is expected to generate substantial indirect benefits to the subjects. The research we will undertake is expected to reveal whether rapid initiation of ART can improve treatment outcomes at a cost that is affordable for treatment service providers and funding agencies. The results of the study may thus lead to improvements in HIV care and keep patients alive and in care longer. The results will also provide evidence about the feasibility of test-and-treat strategies and thus contribute to efforts to improve HIV prevention.

#### *12b iii. Ratio of benefits to risks*

The knowledge to be generated by this study will allow HIV treatment programs to identify whether rapid ART initiation is both effective and cost-effective. This study will address an important gap in the current knowledge around ART initiation and what can be done to reduce the already high proportion of patients who are being lost from care after testing positive. There is currently almost no information available on how to reduce these pre-ART losses. As explained in the previous section, we believe that the risk to subjects in our study is minimal and is outweighed by the indirect benefits and the potential importance of the findings.

#### 12c. Costs and payments to subjects

There will be no costs to subjects for participating in this study.

Subjects in Track 1 who consent to participate and complete the study questionnaire will receive a payment of R100 (approximately \$12.50) to reimburse for their time and inconvenience. This payment will be made in the form of a voucher for a nearby supermarket or cell phone air time.

Subjects in the prospective group of Track 2 who consent to participate and complete the study questionnaire will receive a payment of R50 (approximately \$6.25) to reimburse for their time and inconvenience. This payment will be made in the form of a voucher for a nearby supermarket or cell phone air time.

Subjects in the retrospective group of Track 2 and the retrospective comparison group of Track 1 (retrospective record review only) will not receive any payment.

#### 12d. Recruitment

Identification of potential subjects will occur during HIV post-test counseling, blood draw for CD4 count, return of CD4 count results, or first HIV-positive antenatal visit. All of these activities are conducted within the study site's VCT area. In the VCT waiting area and the clinic's main reception area, a flier will be posted that informs patients that a study is underway and indicates where to get further information. A short pamphlet will be distributed to patients requesting further information. The flier and pamphlet will be translated into the commonly used languages at the study site.

The site's post-test counselors, nurses, and registration staff and the study assistant will inform potentially eligible patients about the study while they are awaiting and/or receiving services. They will explain that a study is underway and that patients who voluntarily consent to participate in the study and are found to be eligible for ART may have the opportunity to initiate treatment immediately, rather than following the standard schedule of visits. Patients who indicate that they may be interested in participating in the study will be referred to the study assistant immediately upon completion of the regular post-test counseling, CD4 blood draw, or return of CD4 count results. Those who do not wish to be referred to the study assistant will receive the site's standard pre-ART care.

#### 12e. Informed consent

Written, informed consent will be sought from all study subjects in Track 1 and the prospective group in Track 2. The informed consent information sheet will describe the nature and goals of the study and assure subjects their information will be kept confidential. For Track 1, it will explain to subjects the possible treatment options in the study:

- The consent form will explain that patients who consent to participate in the study but are found to be not yet eligible for ART will not be enrolled in the study. They will be provided with standard pre-ART care by the study site instead.
- For Track 1, the consent form will explain that patients will not get to decide which group they will be in, but rather that we will decide by chance and they will have a 50-50 chance of being in either group. The form will explain that if they are randomized to the group how their care will be different from standard care. It will also explain that any individual patient can choose not to participate in the study and be offered standard initiation.
- For Track 2, the consent form will explain that the study is limited to a questionnaire and medical record review.
- Consent forms will explain about follow-up through medical record data collection.

The consent form will be administered by a trained study assistant and will indicate that the subject gives us permission to access their clinic records. The consent form will also state that the subject agrees to be interviewed using a baseline questionnaire. Participants will be assured that data collected for our study will be kept strictly confidential and will never be reported to clinic staff or anyone outside the study team.

The full informed consent information sheet and form will be translated into the most commonly used languages at the study site. The languages for which translation is expected to be required are Isizulu, Sesotho, and Xitsonga. If other or additional common languages are needed, the form will be translated accordingly. Translated forms and attestations of translation accuracy will be submitted to the IRB prior to any use of the forms. Subjects who unable to read and/or sign the consent form due to illiteracy will be asked to provide a thumbprint mark, in the presence of a witness who will also sign the form. Patients who do not speak English or any of the languages listed above will be regarded as unable to provide written informed consent, which is an exclusion criterion for the study, and will not be eligible for study enrollment.

Consent will be sought after study inclusion/exclusion criteria have been met, with the exception of eligibility for ART, which will only be determined after consent.

A blank consent form addendum will be placed in each Track 1 subject's clinic file to be used if the subject's care is being transferred to another clinic. The addendum will request consent to collect medical record data during the follow up period from the new clinic. It will be administered by study staff only if a transfer is being processed.

Informed consent will not be sought for the retrospective group in Track 2 or the retrospective comparison group in Track 1, for whom the study will be a record review only. Data for these groups will be collected retrospectively, with identifiers retained in a linking file only long enough to allow separate source documents (e.g. PMTCT register, HCT register, pre-ART register, and electronic medical record) to be matched for individuals. The study team will have no interaction with these groups.

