#### *6c ii. TB test*

Sputum samples for patients with TB symptoms will immediately be sent to the on-site laboratory for testing using Xpert MTB/RIF. Each patient will be asked for two sputum samples to allow two Xpert tests to be run. Those with at least one positive Xpert test will be considered to have active TB. Those with two negative tests will be considered not to have TB. Those with inconclusive test results will be diagnosed clinically by the study nurse or the site doctor. Patients diagnosed with TB will be told of their results and escorted by the study assistant to the site's TB clinic, where TB treatment can be initiated.

A third sputum sample for all patients diagnosed with TB will be sent to the off-site National Health Laboratory Service laboratory for smear microscopy and culture if required. The NHLS lab results will be monitored by the study team. Any positive TB diagnosis not already made by the study nurse will be conveyed immediately to the site, and the patient will be contacted by the study assistant and asked to return to the clinic to initiate TB treatment.

The study site's standard procedures will be followed with regard to TB treatment. Under current South African guidelines, two weeks (14 days) of TB treatment is required prior to initiating ART for patients with a CD4 count  $\leq 350$  and eight weeks of TB treatment is required for patients with a CD4 count  $> 350$ . Study subjects diagnosed with TB and with CD4 counts  $\leq 350$  will be asked to return to the clinic between 14 and 28 days after study enrollment to continue with rapid ART initiation. Those returning in more than 28 days will be offered standard ART initiation. Subjects with TB and CD4 counts  $> 350$  will be advised to return for TB treatment only, then continue with standard ART initiation. Patients already on TB treatment but for less than 14 days at the time of study enrollment will also be asked to return once they have reached 14 days of TB treatment.

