Medical record data for study subjects will be downloaded from the site's existing electronic medical record system, as described above. Records in this system are created only when patients initiate ART, and thus do not capture pre-ART care (HIV tests, monitoring CD4 counts, etc.). The lead data analyst will be responsible for ensuring that study identification numbers are correctly matched to the record numbers in the MRS. In instances where the data analyst cannot match a study ID number to an electronic medical record number using only the fields in the study linking file, a query will be sent to the on-site study staff, who will access the clinic's paper-based patient files to determine whether the subject ever initiated ART and, if so, locate the correct MRS number.

For subjects in the standard group, eligibility for study enrollment can only be determined once treatment eligibility is established by CD4 count or other criterion. For these subjects, the study team will review the site's paper-based patient files on a monthly basis to determine whether and when the subject has been found eligible for treatment and if treatment has been initiated. This information will be entered onto case report forms and captured in the REDCap database as described above.

A note or tab indicating that a patient is a participant in the study will be attached to the cover of each subject's paper medical record at the study site, to assist site and study staff in locating study subjects' files should this be necessary and to ensure that site staff are aware of which patients are study participants.

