#### *8f iv. Aggregate statistics*

Subjects who consent to study participation but are not eligible for ART and those who are found to be study ineligible for any other reason will not be enrolled in the study, as explained above. These subjects' ineligibility for the study will be confirmed by the lead data analyst. Data already collected for these subjects will be used to compile aggregate information on a monthly basis regarding patients at this site who are not eligible for treatment (e.g. average age and average CD4 count of patients who test HIV-positive). Individual data will be destroyed at the end of each month following compilation of the monthly aggregate statistics. Source documents for any test results (CD4 count, TB test result) generated during screening procedures will be retained in the study clinic's file for the patient.

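### The assurance in 12e that study data never reach clinic staff contradicts the loss referral in 12a i and the TB notification in 6c ii

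*Protocol*

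**What the plan says.** Section 12e (Informed consent) describes what participants will be told: that data collected for the study "will be kept strictly confidential and will never be reported to clinic staff or anyone outside the study team". Section 12a iii repeats the rule from the staff side. Study staff are to be trained not to disclose information collected in the study to anyone outside the study team.

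Section 12a i (Loss to HIV care, Protection) sets out the safeguard for subjects who drop out. It says "The study site maintains a small team of loss-to-follow-up counselors", notes that these counselors do not always learn in time who has been lost, and continues: "As we will be generating this data, we will work alongside to the counselors". The stated aim is that the counselors hold current information on each subject's status. It then commits that "we will ensure that all patients defined as lost to follow up at their 6-month viral load monitoring visit", or by 10 months after enrollment, are referred to them for contact.

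Section 6c ii (TB test) has the study team monitor results from the off-site national laboratory and says: "Any positive TB diagnosis not already made by the study nurse will be conveyed immediately to the site".

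Section 6e ii (Medical record follow up) adds a note in the subject's clinic file, addressed to clinic staff, when the study's review finds that no 6-month viral load was done.

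**The concern.** The assurance names clinic staff as people who will never receive study data. The procedures name the site and its counselors as people who will. A study assistant trained under 12a iii has one rule that forbids the transfer and another that orders it.

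Section 12a lists loss to HIV care and breach of confidentiality among the study's four risks. As written, carrying out the protection against the first departs from the protection promised against the second. Section 12a iii also says that stigma still inhibits disclosure of HIV status in this population, so who sees the data is likely to matter to someone deciding whether to consent.

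**Working it through.** The plan has no figure to reproduce here. The check is a comparison of sections.

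1. **What the assurance covers.** It refers to data collected for the study. Section 8a lists four sources of such data: the screening form, the case report form, medical records abstracted by the study, and the pre-screening notebook. Section 8c puts laboratory results on the Track 1 case report form. The covered data therefore extend well beyond questionnaire answers.

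2. **Who counts as clinic staff.** Section 12a i says the site maintains the loss counselors. They are not part of the study team described in section 9.

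3. **Loss status.** Section 12a i says the study generates the information on who is lost, and that the counselors lack it in timely form. Giving it to them, subject by subject, reports study data to clinic staff. This conflicts directly with 12e.

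4. **TB diagnoses.** Section 6c ii has the study team find the result and convey it to the site. This also conflicts with 12e, though the result comes from the national laboratory and concerns a patient of the site.

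5. **Missing viral load.** The note under 6e ii tells clinic staff what the study's record review found. It carries little information, so it is a lesser instance of the same conflict.

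6. **Whether an exception appears elsewhere.** None was found. The permission in 12e to use clinic records lets information pass from the clinic to the study, not back. Neither 12a iii nor 12f provides for release to clinic staff for care.

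7. **The linking file.** Section 12a iii limits this file to matching study numbers with electronic records and, for verification and completion of data, with paper files and source documents. Section 12f strips identifiers from downloaded clinical data. If lost subjects are identified from those data, naming them to the counselors means going back through the linking file, which is not a listed use.

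8. **Who receives the assurance.** Under 12e, consent is sought in Track 1 and in the prospective group of Track 2. The table in section 10 plans 600 and 153 consents, and 600 + 153 = 753. That is the number who would hear the promise, not the number whose information would be passed on. The timed loss referral is defined by Track 1 endpoints, and the TB notification sits in the rapid group's procedures. The general commitment in 12a i to keep counselors informed of subjects' status is not limited to one track.

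**The case against.** The best defense is that the assurance means questionnaire answers only. It closely follows the sentence on the baseline questionnaire. Section 12a says the only new data apart from routine records will be questionnaire responses, and 12g says that safety data after treatment initiation are generated by the site. On that view, clinical results and visit history already belong to the clinic. This does not rescue the wording. The assurance concerns what the study collects, section 8a counts abstracted records and the case report form as collected data, and 12a i itself says the study generates the loss information. What stands is that much of what is shared comes from records the site could hold anyway, so the practical breach is smaller than the words suggest.

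A second defense is that the operating instructions are explicit, so staff would follow them. That is probably true. It makes a withheld TB result or referral unlikely, but leaves the assurance untrue.

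A reader might infer more than the documents support:

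- **More breaches.** Section 8f ii says "A note or tab indicating that a patient is a participant in the study will be attached to the cover" of the paper record, and 8f iv says source documents for test results "generated during screening procedures will be retained in the study clinic"'s file. The first marks participation, and site staff refer patients to the study themselves (6b i). The second, like the printouts in 8f ii, is largely ordinary clinic record-keeping. Neither is relied on here.
- **Everyone affected.** Planned Track 1 consents number 600, but standard-group CD4 results come from the clinic's own blood draw and usual laboratory route (6b iv, 6d i). The study discloses nothing by them.
- **A count from the planning rates.** With 400 enrolled, or 200 per group, and 50% and 70% success (section 10), expected failures are 200 × (1 − 0.50) + 200 × (1 − 0.70) = 100 + 60 = 160. These are failures on the primary outcome. Under 11a i they include subjects in care but unsuppressed and anyone without a viral load for any reason. Section 8e defines loss separately, as being more than one month late for the last medication pickup, and the protocol plans no loss rate. The 160 does not measure referrals.
- **Invalid consent.** The consent form is not in the text supplied and may already state exceptions. Nothing can be concluded about the validity of consent.

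**Conclusion.** The contradiction holds. An assurance without exceptions in 12e, and the matching staff rule in 12a iii, cannot both stand with the loss referral in 12a i and the TB notification in 6c ii. The note under 6e ii adds to it slightly. The clearest conflict is with 12a i, where the protocol itself calls the information study-generated and the recipients are site employees.

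The size is modest. It is a false statement about participant protection, correctable by rewording, with no effect on outcomes, analysis or sample size. The number of subjects whose information would be shared cannot be derived from the protocol. The conclusion assumes that section 12e describes fairly what participants are told, and that loss status is passed on for identifiable individuals, as referral for contact requires.

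**What to change.** Reconcile the sections as follows:

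- In 12e, replace the absolute assurance. State that questionnaire answers and research files stay within the study team, and that loss-to-care status and test results needed for care are shared with clinic staff as described in 6c ii, 6e ii and 12a i. Change the consent information sheet only if it carries the same promise.
- In 12a iii, add the same exception to the staff non-disclosure rule.
- In 12a iii, add referral of lost subjects to the permitted uses of the linking file, if that file is used to identify them.

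The cost is a few sentences, translation of any changed consent wording, and ethics resubmission. A few more candidates may decline once told that some information reaches clinic staff. No procedure, endpoint or analysis needs to change.
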